#### Exercise MRI

Physiologic reserve refers to capacity for augmented function, beyond resting function, in organs and biological systems. A gradual decline in physiologic reserve of all tissues and organ systems is a hallmark of aging and many chronic diseases [43, 44]. Chemotherapy has the potential to rapidly accelerate this decline. For example, it has been reported that the cardiorespiratory fitness reserve capacity of one-third of breast cancer survivors is less than that required for independent living during or after treatment [45]. The proposed MRI-derived measures in the current study utilize this concept of using exercise stress to assess change in physiologic reserve capacity of the heart and skeletal muscle.

Cardiac, aortic, and skeletal muscle structure and function will be assessed via MRI (Prisma 3.0 Tesla, Siemens, Erlangen, Germany) at the Peter S. Allen MR Research Centre (Edmonton, Alberta) and custom analysis with Matlab software (Mathworks Inc., Natick, MA). Cardiac and muscle reserve function will be assessed using a commercially available, MRI-compatible ergometer with two modules designed for exercise testing within the scanner bore (Ergospect, Innsbruck, Austria) (Fig. 2). The ‘Cardiostep module’ is a horizontal resisted stepping device (Fig. 2A) that can be used for whole body exercise to increase central hemodynamics and augment cardiac function. The ‘Trispect module’ is a resisted plantar flexion (i.e., toe pointing) device (Fig. 2B) that can be used to exercise the muscle of one lower leg to allow for evaluation of skeletal muscle function independent of cardiac function.

**Fig. 2 Fig2:**
[figure not shown]
Ergospect ergometers made for use inside MRI scanner bore for whole body exercise (**a**) and isolated calf skeletal muscle exercise (**b**)

#### MRI protocol

The MRI protocol is summarized in Fig. 3. The MRI protocol starts with quantification of skeletal muscle mass of the right lower leg and thigh using a Dixon fat-water separation acquisition method [46] that enables precise and reproducible segmentation of skeletal muscle and adipose tissue. Next, time-resolved phase contrast and oxygen concentration sensitive images were acquired to quantify resting blood flow and venous oxygen saturation (S_v_O_2_), respectively, in the superficial femoral vein of the right leg, similar to that previously described [47]. S_v_O_2_ is quantified via susceptometry-based oximetry using deoxyhemoglobin as an intrinsic contrast agent. Together with arterial oxygen saturation and measured hemoglobin concentration, the volume of oxygen consumption (VO_2_) can be calculated for the right lower leg skeletal muscle, indexed to lower leg muscle mass (mL/min/kg), as: lower leg VO_2_ = blood flow*(S_a_O_2_ – S_v_O_2_)* [Hb]*Ca; where: S_a_O_2_ = arterial oxygen saturation from pulse oximeter, [Hb] = hemoglobin concentration, Ca = hemoglobin oxygen carrying capacity (1.34 mL O_2_/g Hb). Hemoglobin concentration corresponding to pre- and post-anthracycline treatment will be extracted from clinical records. If no recent clinical measure of hemoglobin is available for the one-year follow-up assessment then it will be measured as part of the study. Following resting evaluation, the right leg performs plantar flexion exercise on the Trispect module for four minutes at 8 watts. This wattage was chosen as it was equivalent to 60% of the average peak wattage attained in pilot testing of a maximal incremental plantar flexion test in *n* = 20 of the same population. Heart rate and rating of perceived exertion will be recorded every minute using an index finger pulse oximeter and self-report, respectively, while brachial blood pressure will be measured every two minutes. Flow and S_v_O_2_ imaging, identical to the resting evaluation, will commence immediately upon discontinuation of exercise to capture the peak and four minutes of recovery data for blood flow and S_v_O_2_. Images are repeated every 3.4 s.

**Fig. 3 Fig3:**
[figure not shown]
MRI protocol

Following 10 min of rest, resting cardiac and vascular structure and function are assessed. ECG-gated, end-expiration breath-hold techniques will be used to acquire single cardiac cycle transverse images of the ascending and descending aorta. Brachial pulse pressure will be assessed twice, 60 s apart at the time of aortic imaging to calculate aortic distensbility as change in cross-sectional area of the aorta divided by pulse pressure. Myocardial T1 mapping will be acquired in two mid-ventricular short axis slices using both SASHA [48] and MOLLI [49] approaches. A free-breathing real-time cine imaging approach will be used to acquire parallel short-axis slices throughout the LV, as well as 4- and 2-chamber long axis images [50]. Full coverage of the LV long and short axis is achieved in ~ 45 s. This technique is ideal for exercise as it does not require ECG gating and removes the requirement for breath holding during image acquisition. The Cardiostep exercise protocol will start at 20 watts and increase by 5 watts every 15 s until volitional exhaustion. The exercise will take place within the scanner bore with a study staff member inside the scanner room to encourage the participant and record a rating of perceived exertion (0–10) every minute. Acquisitions will be performed at rest and immediately upon attainment of peak exercise. LVEF will be calculated as: (end-diastolic volume – end-systolic volume) / end-diastolic volume, using custom post-processing Matlab software.

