### Outcome measures

The study outcome measures and their timing are summarized in Table 2. The primary outcome measure is cardiac function reserve capacity (LVEF reserve), which is calculated as peak exercise LVEF – resting LVEF, at the end of anthracycline treatment relative to the control group. Despite being the primary parameter used to diagnose cardiotoxicity, it is recognized that resting LVEF is insensitive to subclinical anthracycline-related cardiac damage due to the heart’s capacity to compensate for dysfunction at rest. By the time a decrease in resting LVEF is realized, there is likely already substantial and irreversible damage to the myocardium [3]. In women previously treated for breast cancer, a systematic review demonstrated that the application of either exercise or pharmacological stress during cardiac imaging techniques identified cases of cardiac dysfunction that were not identified using resting imaging [41]. More specifically, in women receiving anthracycline treatment for breast cancer, LVEF reserve (peak – rest) and peak LVEF after two treatments were significant predictors of a resting LVEF drop to < 50% at 18 months after treatment [42].

**Table 2 Tab2:** Summary of study outcome measures

Measure	Assessment Method	72+ h pre-anth	24 h post 1st & last anth	2–3 w post last anth	1 y post 1st anth	5 y post 1st anth
Primary Outcome:						
LVEF reserve (peak – rest)	MRI	x		x	x	
Secondary Cardiac Outcomes:						
Peak and resting LVEF	MRI	x		x	x	
Resting and peak LV strain	MRI	x		x	x	
LV volumes and cardiac output	MRI	x		x	x	
Myocardial T1	MRI	x		x	x	
LV mass	MRI	x		x	x	
NT-proBNP	Venipuncture	x	x	x		
Secondary Vascular Outcome:						
Ascending and descending aortic distensibility	MRI	x		x	x	
Secondary Skeletal Muscle Outcomes:						
Lower leg oxygen extraction	MRI	x		x	x	
Lower leg oxygen consumption	MRI	x		x	x	
Thigh muscle mass	MRI	x		x	x	
Thigh muscle quality	MRI	x		x	x	
Secondary Integrative Outcomes:						
Whole body oxygen consumption reserve	CPET	x		x	x	
Treatment symptoms	Rotterdam Symptom Checklist	x		x	x	
Exploratory Outcomes:						
Tumor size	Ultrasound	x		x^a^		
Quality of life	FACT-General questionnaire	x		x	x	
Fatigue	FACT-Fatigue questionnaire	x		x	x	
Markers of oxidative stress/antioxidants	Venipuncture	x		x		
Clinical Outcomes					x	x
Safety Outcomes:						
Clinically reported symptoms	ESAS	Will be extracted from clinical records for intervention period				

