Intervention-related symptoms or adverse events	Food diary, Exercise session log	Will be collected for each intervention delivered				

*anth* anthracycline chemotherapy treatment, *CPET* cardiopulmonary exercise test, *ESAS* Edmonton Symptom Assessment System, *LVEF* left ventricular ejection fraction

^a^Typically measured before and after completion of all chemotherapy as standard of care

Secondary outcome measures include other parameters of cardiac function and structure (LV resting and peak strain, myocardial T1, LV volumes and mass, resting and peak cardiac output, peak LVEF, resting LVEF) and aortic distensibility at the end of anthracycline treatment, as well as circulating NT-proBNP at 24 h post the first and last treatment. Secondary skeletal muscle outcome measures include lower leg oxygen consumption and extraction, and thigh mass and quality at the end of anthracycline treatment. Secondary integrative outcome measures include whole body oxygen consumption reserve and treatment symptoms. Both interventions are hypothesized to reduce toxic effects on the heart, aorta, skeletal muscle and integrative measures relative to usual care.

A number of additional outcome measures of interest will be collected that are designated as exploratory. Exploratory outcomes at end of treatment include: 1) tumor size in neoadjuvant patients; 2) patient-reported quality of life and fatigue; 3) circulating markers of oxidative stress and antioxidants. To assess for potential longer-term effects of the interventions, a one-year follow-up with assessment of all MRI and questionnaire measures as well as CPETs and clinical outcomes (e.g. cancer recurrence, cardiac events, hospitalizations, mortality) will be completed. These combined clinical outcomes will also be collected as exploratory outcomes after five years of follow-up.

Safety outcomes will include clinically reported Edmonton Symptom Assessment scores throughout the intervention period as well as intervention-related symptoms or adverse events collected via food diaries and supervised exercise session monitoring.

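### The printed formula for aortic distensibility has no division by starting area, so as written it defines aortic compliance, which scales with vessel size

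*Protocol article*

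**What the plan says.** In the MRI protocol section of the Protocol article, the aortic measurement is described in two steps. Breath-hold techniques are used to "acquire single cardiac cycle transverse images of the ascending and descending aorta". Then "Brachial pulse pressure will be assessed twice, 60 s apart at the time of aortic imaging", in order to "calculate aortic distensbility as change in cross-sectional area of the aorta divided by pulse pressure".

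Table 2 has a single line under its secondary vascular heading, "Ascending and descending aortic distensibility". It is measured before anthracyclines, 2–3 weeks after the last dose, and one year after the first. The Outcome measures text confirms the status: "aortic distensibility at the end of anthracycline treatment" is a secondary outcome. No other place in the article gives a formula for it.

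**The concern.** The name and the formula do not describe the same quantity. Distensibility is the relative change in area per unit of pressure. The printed formula takes the absolute change per unit of pressure, which is compliance.

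Anyone who programmes the outcome from this sentence would report compliance under the name distensibility. The values could not be compared or pooled with distensibility from other studies. They would also depend on how large each woman's aorta is, as well as on how it behaves under pressure. The study's aims cover heart, aorta and skeletal muscle, and the aortic part rests on this one measure, taken at two sites.

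**Working it through.** The documents give no numerical figure for this outcome, so there is nothing to reproduce. The check is dimensional, with an illustration.

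**Inputs from the Protocol article**
- Numerator: change in aortic cross-sectional area, ΔA (MRI protocol).
- Denominator: brachial pulse pressure, PP (MRI protocol).
- Starting area, A₀: not in the formula, but obtainable from the single-cycle images.

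**Inputs assumed for illustration (not in the documents)**
- PP = 40 mmHg.
- Relative area change ΔA/A₀ = 20%.
- Aortic diameter d from 20 to 35 mm.

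**Step 1. Units.**
- As printed: C = ΔA / PP, in mm²/mmHg (compliance).
- Distensibility: D = ΔA / (A₀ × PP), in 1/mmHg.
- Hence C = D × A₀. The printed quantity is distensibility multiplied by starting area.

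**Step 2. Same wall behaviour, different vessel size.** With A₀ = πd²/4 and ΔA = 0.20 × A₀:

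| d (mm) | A₀ (mm²) | C = ΔA/PP (mm²/mmHg) | D = ΔA/(A₀ × PP) (per mmHg) |
|---|---|---|---|
| 20 | 314.2 | 1.57 | 5.0 × 10⁻³ |
| 25 | 490.9 | 2.45 | 5.0 × 10⁻³ |
| 30 | 706.9 | 3.53 | 5.0 × 10⁻³ |
| 35 | 962.1 | 4.81 | 5.0 × 10⁻³ |

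The printed formula varies by 4.81 / 1.57 ≈ 3.1-fold through size alone. D does not vary.

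**Step 3. Same woman over time.** Start at d = 25 mm, so that ΔA = 0.20 × 490.9 = 98.2 mm². Hold ΔA and PP fixed and let A₀ rise:

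| Rise in A₀ | C (mm²/mmHg) | D (per mmHg) |
|---|---|---|
| 0% | 2.45 | 5.00 × 10⁻³ |
| 5% | 2.45 | 4.76 × 10⁻³ |
| 10% | 2.45 | 4.55 × 10⁻³ |

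In this example compliance shows no change while distensibility falls. A within-person comparison therefore does not make the two interchangeable.

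**Step 4. Changes also scale with size.** If A₀ is stable, change in C = A₀ × change in D. The same change in distensibility thus counts about 3.1 times as much in a 35 mm aorta as in a 20 mm one (962.1 / 314.2).

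**Step 5. Comparison within the section.** LVEF is written with its normalising term: "end-diastolic volume – end-systolic volume) / end-diastolic volume". Lower-leg oxygen consumption is also stated to be indexed to muscle mass. The article does give normalising terms for other measures in the same section, so a reader has no reason to supply one for the aorta.

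**The case against.** The best defence is that this is condensed wording. The phrase sits in a clause explaining why pulse pressure is taken and is not set out as an equation. The outcome is called distensibility wherever it appears, the images give the starting area, and a journal article shortens the full protocol. Change may simply mean relative change. This stands as far as intent goes: the documents do not show that a wrong computation is planned. It does not remove the point, because the article does commit to a formula and nothing in it corrects that formula.

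A reader might go further and infer that vessel size adds noise and costs power. The documents do not support that. Suppose, purely as assumptions, that distensibility has a coefficient of variation of 40% and starting area one of 15%, 20% or 25%, with the two lognormal and independent. The relative variance of the product is then (1.16 × (1 + c²) − 1) / 0.16 times that of distensibility, where c is the coefficient of variation of area. This gives 1.16, 1.29 and 1.45. Under the same model the inflation vanishes at log-scale correlations between area and distensibility of about −0.19, −0.26 and −0.32, and at −0.4 the ratio is 0.83 to 0.89. The documents give no correlation, so even the direction is open.

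These are also cross-sectional variances. The Statistical analyses section plans a linear mixed model with random effects on repeated measures, which would absorb part of any stable size difference between patients.

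Nor should a reader infer a biased group comparison: randomisation means that vessel size does not systematically favour an arm. That ascending and descending values would lie on different scales matters little, since the article neither pools nor compares the sites.

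**Conclusion.** The point holds as a misstatement of an outcome definition. Read as written, the formula gives compliance, which is proportional to starting area for a given distensibility and can part from distensibility over time if that area changes. This follows from the units alone. The 3.1-fold spread and the 5% and 10% examples are illustrations that rest on the assumed diameters, pulse pressure and area change.

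The reach is limited to the only secondary vascular outcome, at its two sites. The primary outcome (LVEF reserve), the sample size and the interim analysis of resting LVEF are untouched. If the wording is shorthand, only the text needs correcting. No variance inflation or loss of power is claimed.

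**What to change.** State in the MRI protocol section, and wherever the outcome is programmed, that for the ascending and descending aorta separately:

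distensibility = (maximum area − minimum area) / (minimum area × pulse pressure), in units of 1/mmHg.

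If the unnormalised quantity is also wanted, report it in addition under the name aortic compliance, in mm²/mmHg.

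The cost is one line of text and a check of the analysis code. Both areas can be read from the aortic images already planned, so no new measurement or visit is needed, and the change can be made before analysis.

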#### Cardiopulmonary exercise testing

The integrated effect of impaired reserve function in the heart, vascular, and skeletal muscle systems is reduced cardiorespiratory fitness, measured as peak whole body oxygen consumption reserve (VO_2_R). VO_2_R will be measured using the gold standard cardiopulmonary exercise test (CPET). A modified Balke or Bruce treadmill protocol will be utilized until volitional exhaustion or other indications for termination [51]. Choice of protocol is based upon baseline fitness and simultaneous enrolment in an observational study using the Bruce protocol; and will be kept consistent within a given participant over time. Continuous expired gases and heart rate will be measured with a calibrated TrueOne 2400 metabolic cart (Parvo Medics, Sandy, UT). The highest volume of oxygen consumed during a 20-s period minus resting oxygen consumption will be taken as VO_2_R. The test will be performed according to the American College of Sports Medicine guidelines by an exercise physiologist [51]. The CPET will be performed on a separate day from the MRI or on the same day but with at least one hour of rest after completion of the MRI scan. Similar timing between MRI and CPET will be used for follow-up assessments for each participant. The baseline CPET will be performed at least 72 h in advance of the first treatment.

#### Circulating biomarkers

Levels of the N-terminal prohormone of BNP (NT-proBNP) after the first anthracycline treatment, as well as persistent elevations at 24 h after multiple treatments are predictive of a significant reduction of LVEF over time [52, 53]. NT-proBNP will be assessed at study enrolment, at 24–28 h after the first and last anthracycline treatment, as well as end of anthracycline treatment. Venipunctures will always be performed prior to the MRI and CPET such that results will not be influenced by exercise. NT-proBNP will be assessed in serum via electrochemiluminescence sandwich immunoassays (Roche Diagnostics, Laval, Quebec) by an accredited hospital laboratory.

A reduction in oxidative stress and increase in antioxidants are the primary mechanism hypothesized in exercise cardio-protection [17]. As an exploratory outcome, serum from study enrolment and end of treatment will also be stored at − 80° at the Canadian Biospecimen Repository (Edmonton, Alberta) for batch analysis of markers of oxidative stress and antioxidants. Specific assays/markers will be chosen upon completion of the study to ensure use of the most modern assays.

#### Questionnaires

Patient-reported outcomes will be assessed with instruments validated for use in cancer populations. Quality of life and fatigue will be assessed by the Functional Assessment of Cancer Therapy (FACT)– General and FACT-Fatigue [54], respectively. Treatment symptoms will be assessed by the Rotterdam Symptom Checklist [55].

#### Clinical data

Clinical data that will be extracted from patient records for study use will include ultrasound-assessed tumor size (in neoadjuvant patients only), anthracycline dose received, relative dose intensity, Edmonton Symptom Assessment System responses, hemoglobin, hematocrit, other prescribed drugs, cancer or cardiac events, hospitalizations, and mortality. This data will be collected for participants who discontinue or deviate from intervention protocols.

#### Data management

All research data will be de-identified using a random study ID, and will be securely stored with access provided to study staff and investigators only. All data that requires electronic entry will be double-checked for accuracy.

### Interventions

Caloric restriction intervention: Participants who are randomized to the caloric restriction arm will receive 48 h worth of prepared meals consisting of 50% of their daily caloric requirement. Caloric needs will be measured using resting energy expenditure (REE) assessed at baseline using indirect calorimetry in the morning after a 10–12 h water-only fast. Total daily energy expenditure will be calculated as REE multiplied by 1.4, which accounts for a low level of physical activity [56]. Participants will choose three isocaloric meals and two snacks consisting of half of the calories provided in the meals from a prepared menu with several options. Food will be freshly prepared within a day of the intervention for each participant at a metabolic kitchen, with each ingredient weighed to one-tenth of a gram. Each meal and snack will consist of North American macronutrient composition guidelines (30% protein, 20% fat, 50% carbohydrates) [57] calculated using Food Processor SQL (v11.0.3; ESHA Research, Salem, OR), and will be individually packaged and labelled. All food to be consumed within the 48 h period will be packed into an insulated cooler to be picked up by or delivered to the participant. To track adherence and adverse events, participants will be asked to keep a food diary to record any dietary deviations, as well as whether they experience any adverse nutrition impact symptoms (e.g., light-headedness, dizziness, nausea, diarrhoea).

Exercise intervention: Participants who are randomized to the exercise arm will perform a single bout of supervised aerobic exercise scheduled such that it would end approximately 24 h prior (window of 22–26 h allowed) to each of their scheduled anthracycline treatment times. The session will consist of a 10-min warm-up, 30 min performed at 70–75% of measured heart rate reserve, which corresponds to a vigorous intensity [51], followed by a 5-min cool-down. As an adjunct method of exercise prescription, the intensity will be adjusted as needed to maintain a minimum rating of perceived exertion (Borg 6–20 scale) of 13 (“somewhat hard”) and a maximum of 17 (“very hard”). An exercise physiologist will supervise the session one-on-one and will document any exercise-related symptoms or major adverse events.

Usual care: As there are currently no clinical guidelines or recommendations on exercise timing or calorie reduction in relation to chemotherapy treatment, standard oncology care recommendations to maintain a pre-diagnosis exercise routine and diet throughout treatment was chosen as the comparator. Participants in this group will receive a phone call from study staff during each anthracycline treatment cycle to maintain engagement and enhance retention.

There may be potential for the two interventions to have a synergistic effect on our outcomes if they were combined. However, evaluating the independent impact, safety and efficacy of a caloric restriction versus an exercise intervention in humans is essential prior to combining these interventions. All participants will be asked to restrict any exercise performed on their own to light to moderate intensity for the 72 h prior and also for 48 h after each anthracycline treatment to isolate the effect of the pre-treatment exercise intervention. Compliance with this restriction will be assessed using a modified version of the Godin Leisure Time Exercise Questionnaire [58] for each treatment. Overall physical activity and dietary intake for the duration of the intervention period (~ 3 months) will be quantified and compared between groups by self-report using the Recent Physical Activity Questionnaire [59] and the Block Brief 2000 Food Frequency Questionnaire (Nutrition Quest, Berkley, CA). These questionnaires will also be administered at study entry and one-year follow-up with reference to their habits over the previous three months.

